#### Methods for additional analyses (such as subgroup analyses) {20b}

There will be no additional analyses in this trial.

#### Methods in analysis to handle protocol non-adherence and any statistical methods to handle missing data {20c}

In case of missing data, an intention-to-treat analysis will be performed. For primary endpoint, for patients who are lost to follow-up, censored data will be the date of last follow-up. For secondary endpoints, all patients will have regular follow-up in the outpatient department and also be contacted by the CRC of this trial. Therefore, the data could be well collected as expected.

#### Plans to give access to the full protocol, participant-level data, and statistical code {31c}

All participating centers have access to the full protocol, participant-level dataset, and statistical code. The datasets analyzed during the present study are available from the corresponding author on reasonable request.

### Oversight and monitoring

#### Composition of the coordinating center and trial steering committee {5d}

Standard Protocol Items: Recommendations for Interventional Trials (SPIRIT) guidance: Composition, roles, and responsibilities of the coordinating center, steering committee, endpoint adjudication committee, data management team, and other individuals or groups overseeing the trial (if applicable). See Item 21a for the data monitoring committee (DMC).

A trial steering committee (TSC) was set up before the start of the trial. The TSC in this trial consists of the president of Shanghai Chest Hospital ([name]) and [name], who act as a body that takes responsibility for the scientific integrity of a clinical trial, assessment of study quality and conduct, and the scientific quality of the final study report.

[name] will be responsible for all aspects of local organization, including identifying potential recruits and taking consent. [name] is supervising the trial and they will meet every two weeks to discuss the progress of this trial. Also, [name] will hold online or face-to face meetings for investigators from all participating centers every three months to oversee conduct and progress.

#### Composition of the data monitoring committee, its role and reporting structure {21a}

A DMC has been established parallel to the finish of study protocol. In our study, the DMC consists of three experts: one thoracic surgeon ([name]), one radiologist ([name]), and a pathologist ([name]) from Shanghai Chest Hospital. The DMC should consider essential parts of study conduct such as protocol adherence and patient withdrawal. In most cases, safety monitoring, especially for severe adverse events, will be the major task for a DMC. Importantly, if major problems with the study conduct are observed, a DMC should consider possible recommendations to the sponsor to improve the quality of the study.

#### Adverse event reporting and harms {22}

Adverse events are defined as any undesirable experience occurring to a subject during the study, regardless of whether they are considered to be related to the treatment procedures. All adverse events reported spontaneously by the subject or observed by the investigator or his or her staff will be recorded during the period of study.

#### Frequency and plans for auditing trial conduct {23}

The project management group will audit this trial every three months, and the process will be entirely independent from investigators and the sponsor. Every three months, they will review the progress of the trial through the online electronic database system, which will be established before the start of this trial, and they will also hold meetings for all principal investigators (PIs) every six months. The trial steering group and the independent data monitoring and ethics committee meet to review conduct throughout the trial period.

#### Plans for communicating important protocol amendments to relevant parties (such as trial participants and ethics committees) {25}

If the protocol needs to be modified, the PI ([name]) will set up a discussion meeting with all investigators in all three centers. The deviations we discuss in the meeting will be recorded as a breach report form. The PI will first notify the funder of this trial of any deviation of the protocol and the reason for that. After granting the permission of the funder, the PI will notify all investigators and a copy of the revised protocol will be sent to the PI to add to the investigator site file. Meanwhile, the revised protocol will be updated in ClinicalTrials.gov, NCT04135664.

#### Dissemination plans {31a}

Authorship eligibility guidelines will follow International Committee of Medical Journal Editors guidelines. The final trial dataset will be available to the investigative team and on reasonable request.

## Discussion

In an increasing numbers of patients, superficial lesions are treated primary with ER after receiving lymph node and distant metastasis evaluation. However, the treatment choice will face a dilemma between esophagectomy and dCRT when the pathology of ER specimen reveals submucosal invasion, which is an increasingly common clinical problem [24]. In the past, the selection was based on the preferences of patient and doctor. Although previous retrospective studies have confirmed that adjuvant chemotherapy or surgery can achieve comparable long-term survival outcomes, small sample size and low proportion of pT1b patients reduced the credibility of evidence [14, 16]. The present study is the first prospective randomized controlled clinical trial to compare the salvage esophagectomy and dCRT for patients with cN0-pT1b ESCC after ESD. Our results will provide high-level evidence to establish an appropriate treatment strategy for these patients.

Superficial esophageal cancer is defined as tumor invaded into mucosal and submucosal lesion. In the retrospective studies, tumor invaded into muscular mucosal (M3) and submucosal (SM) layers are usually treated in the same way because of the high rate of lymph node metastasis [25]. However, we selected T1b as the study subject and excluded M3 patients in this trial, which is based mainly on the following considerations. First, it is difficult to be recruited since the majority of patients with mucosal myometrium after R0 resection in China will choose surveillance. Second, in this trial, we set very strict clinical evaluation criteria for lymph node status, which greatly reduced the probability of occurrence of high-risk M3, so there is no need for adjuvant therapy. Therefore, the T1b patients after ESD were selected as the study subjects.

In this trial design, we did not exclude patients with a positive lateral resection margin. Previous studies have confirmed that the tumor invasion within the submucosa can be well controlled by radiotherapy, and so for the residual lesions in the lateral resection margin after ESD, subsequent adjuvant chemoradiotherapy or surgery is sufficient to obtain local radical treatment [26]. Therefore, those patients do not need to be excluded, which was also consistent with the JCOG0508 study [16]. However, because the tumor has invaded into the muscular layer (T2), patients with a positive vertical resection margin will not be recruited.

For superficial lesions, the lymph node metastasis is balanced upward and downward. In our retrospective study, it can be found that the metastasis rates of the upper mediastinum and the left gastric artery are basically equivalent in the final pathology (data not shown). However, in the long-term follow-up, a high rate of recurrence was found in the upper mediastinum but rarely in the lower mediastinum and abdominal cavity. The results indicate that lymph node recurrence may occur in both upstream and downstream after ESD in early-stage patients. Therefore, the design of radiation target of should cover the longer longitudinal and abdominal cavity, not just the lesion.

However, there are two main limitations of this trial. First, owing to the different interventions, the study is not double-blinded. And the recruitment may be challenging because of the different interventions and cost of treatments. Second, the sample size calculation was based on our clinical observation and the previous report.

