Previous studies have demonstrated that definitive chemoradiotherapy (dCRT) could achieve a survival rate comparable to that of esophagectomy for submucosal esophageal cancer [9]. However, local failure without distant metastasis after dCRT remains a major challenge to achieve long-term survival [10]. Endoscopic resection (ER) has been demonstrated with satisfied control for submucosal esophageal cancer without lymph node metastasis [11]. Therefore, the combination of ER and dCRT conforms to the aim of non-surgical treatment of submucosal esophageal cancer, which can maximize the removal of primary lesions and additional disposition of residual lesions or potential lymph node metastasis [12–14]. The Japan Clinical Oncology Group (JCOG) phase II trial (JCOG0508) was the only prospective clinical study conducted to evaluate the efficiency and safety of combined treatment of ER and CRT for clinical stage I ESCC [15]. The results showed that for patients with pT1b with R0 and pT1a with lymphovascular invasion (+) after ER, the 3-year overall survival (OS) was 90.7% (90% confidence interval 84.0%–94.7%) after prophylactic CRT. They concluded that the combination of ER and selective CRT should be considered as a minimally invasive treatment option for clinical stage I ESCC [16].

Considering the encouraging results of JCOG0508 and other previous studies, we hypothesized that, in comparison with esophagectomy, concurrent dCRT may achieve comparable survival results and better QoL for submucosal esophageal cancer. Therefore, we designed this randomized controlled trial (RCT) to compare the two salvage treatments for pT1b ESCC after ER.

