#### Exclusion criteria

Prior treatment before endoscopic submucosal resection.Inability to accept any treatment component.Prior intervention (surgery, chemoradiation, etc.) for other primary tumor disease.Positive vertical resection margin.Distant metastasis.Inability to understand the informed consent.

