##### Definitive chemoradiotherapy (dCRT)

Radiotherapy will be delivered with photons (6–10 MV) in daily fractions on 5 days per week. Intensity-modulated radiation therapy based on a computed tomography (CT) simulation planning system with 5-mm-thick scan slices throughout the entire neck and thorax and upper abdomen is required.

Target volumes need to be carefully defined.

Gross tumor volume (GTV): The GTV should include the positive margin according to the pathology after ESD.

Clinical target volume (CTV): The CTV is defined as tumor bed and elective lymph node regions. For the proximal third of the esophagus, consider treatment of para-esophageal lymph nodes, bilateral supraclavicular lymph nodes, and mediastinum lymph nodes. For the middle third of the esophagus, consider treatment of para-esophageal lymph nodes. For the distal third of the esophagus, consider para-esophageal, lesser curvature, splenic nodes, and celiac axis nodal regions.

Planning target volume (PTV): The PTV includes PTV-G and PTV-C. Owing to set-up deviation and organ movement, PTV-G is defined as a further 6- to 10-mm expansion to the GTV in all directions and PTV-C is defined as a further 6- to 10-mm expansion to the CTV. The prescribed dose of PTV-G is 6020 cGy (215 cGy/d), PTV-C is 5040 cGy (180 cGy/d), both in 28 fractions.

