### Assignment of interventions: allocation

#### Sequence generation {16a}

The allocation sequence is according to the computer-generated random numbers.

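### Patients with a positive lateral margin are enrolled, but the 90% dCRT rate comes from an R0/pT1a cohort and no margin-adjusted or margin-specific estimate is planned

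*Protocol article*

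**What the plan says.** Eligibility: the only margin that excludes is listed under Exclusion criteria as "Positive vertical resection margin". The Discussion confirms that the other margin was left open on purpose: "In this trial design, we did not exclude patients with a positive lateral resection margin". It describes the tumour there as residual, argues that either trial treatment controls it, and says that admitting these patients agrees with the phase II trial cited as reference 16.

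Treatment: in the dCRT section, "The GTV should include the positive margin according to the pathology after ESD". PTV-G, which is built on the GTV, has its own prescription.

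Design value: Sample size {14} assumes 5-year OS of 75% after esophagectomy and 90% after dCRT, with reference 16 as the source for about 90%. Background and rationale {6a} gives one survival result from that phase II trial, a 3-year OS of 90.7% (90% CI 84.0–94.7%), and gives it "for patients with pT1b with R0 and pT1a with lymphovascular invasion (+) after ER".

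Allocation and analysis: Sequence generation {16a} says "The allocation sequence is according to the computer-generated random numbers" and names no stratification factor. Statistical methods {20a} plans Kaplan–Meier estimates and a log-rank test, again with no factor named. Section {20b}, whose heading mentions subgroup analyses, says "There will be no additional analyses in this trial".

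**The concern.** Two kinds of patient are randomised together. In R0 patients, both treatments deal with possible nodal disease. In lateral-margin-positive patients they must also deal with known residual tumour, which surgery removes and dCRT has to control. The radiation plan differs between the two groups by design. Lateral margin status is therefore a plausible prognostic factor, and it comes from the ESD pathology report that eligibility already requires before randomisation.

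The plan makes no use of it. The primary test is not adjusted for it, and the exclusion of additional analyses removes even a descriptive table. The dCRT rate that sets the sample size is borrowed from a cohort described as R0. That cohort also includes pT1a patients, who are not eligible here, and the reported rate is for 3 years rather than 5. At stake are some precision in the primary comparison, an answer to the obvious question of how margin-positive patients fared, and a power statement that fits the patients enrolled.

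**Working it through.** **1. Reproducing the plan's figure.** Inputs from Sample size {14}: 75% vs 90%, 5% level (sidedness not stated), 80% power, 5% dropout.

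- HR = ln(0.90)/ln(0.75) = 0.366.
- Freedman, one-sided 5%: (1.645 + 0.842)² × [(1 + 0.366)/(1 − 0.366)]² = 28.7, so 29 deaths.
- 29/(0.25 + 0.10) = 82.9, so 83 per group; 83/0.95 = 87.4, so **88 per group**, an exact match.
- Two-sided with fixed 5-year follow-up, the same formula gives 112. Two-sided Freedman with assumed uniform accrual over about 3 years and follow-up of everyone to about 8 years gives 89–90. The article does not say which route was used, so results for both sidedness conventions follow.

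**2. Power for a mixed population.** The article gives neither the margin-positive share *m* nor survival *q* in that group. Assumed: *m* = 10–30%; *q* = 75–85% at 5 years after dCRT; R0 patients at 90%; surgery arm unchanged at 75%.

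- Pooled dCRT rate = 0.90(1 − *m*) + *q m*.
- Evaluable per group = 88 × 0.95 = 83.6.
- Power = Φ(√D × (1 − HR)/(1 + HR) − z), with D = 83.6 × (0.25 + 1 − pooled rate).
- With no mixing, D = 29.26 and power is 81% one-sided, 71% two-sided.
- Example, *m* = 20%, *q* = 75%: pooled rate = 0.90 − 0.20 × 0.15 = 87%; HR = 0.484; D = 31.8; power = Φ(1.959 − 1.645) = 62% one-sided, 50% two-sided.

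| Share | dCRT OS, margin-positive | Pooled dCRT OS | Power, 1-sided | Power, 2-sided | N per group for 80%, 1-sided / 2-sided |
|---|---|---|---|---|---|
| 10% | 85% | 89.5% | 78% | 68% | 96 / 119 |
| 10% | 75% | 88.5% | 72% | 61% | 111 / 143 |
| 20% | 85% | 89.0% | 75% | 64% | 104 / 130 |
| 20% | 75% | 87.0% | 62% | 50% | 145 / 182 |
| 30% | 85% | 88.5% | 72% | 61% | 111 / 143 |
| 30% | 75% | 85.5% | 52% | 40% | 193 / 244 |

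**3. Chance imbalance if allocation is not stratified.** The SD of the between-group difference in share is √(2*m*(1 − *m*)/88), which is 4.5, 6.0 and 6.9 points at 10, 20 and 30%. The 95% ranges are ±8.9, ±11.8 and ±13.5 points. A difference of 10 points or more occurs in about 3, 10 and 15% of trials by normal approximation, and in 2, 13 and 19% with the total number of margin-positive patients fixed. If margin-positive dCRT patients do 15 points worse, a 10-point imbalance moves the contrast by at most 0.10 × 15 = 1.5 points, against a design difference of 15.

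**4. What a margin-specific table could show.** Expected margin-positive deaths, both groups together, at the design rates: 83.6 × *m* × 0.35 = 2.9, 5.9 and 8.8 at 10, 20 and 30%. One-sided power for 75% vs 90% within that group is about 20, 30 and 39%.

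**The case against.** The strongest reply is that the trial's question concerns all randomised cN0-pT1b patients and that randomisation answers it. That stands. A reader might infer that the result cannot be interpreted for either margin group, but the documents do not support this: the pooled comparison is valid for the mixed population, and any imbalance is chance, which the test's error rate already allows for. On the assumptions above its effect is about 1.5 points at most.

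A reader might also infer that allocation is definitely unstratified. The article is condensed and names no factor; it does not say there is none.

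Third, the authors considered the issue. The Discussion gives a reason for expecting local control with either treatment, and the dCRT section includes the margin in the target. Margin status is thus a plausible modifier of the treatment effect, not a demonstrated one. The Discussion's appeal to the phase II trial concerns who may be enrolled and cites no survival figure. Reading it as an error goes too far, because that trial could have enrolled lateral-positive patients while the 90.7% describes only one group of them.

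Last, declining subgroup tests in 176 patients is defensible, and with 3–9 deaths an interaction test would tell nothing. That stands against a formal test. It does not count against a descriptive table, an adjusted primary test or a better-supported design rate.

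**Conclusion.** The point holds as a modest, inexpensive improvement. The article enrols lateral-margin-positive patients, draws the radiation target by that margin, takes its dCRT rate from a 3-year result in R0 and pT1a patients, names no margin stratification and rules out any additional analysis. The loss is some precision in the main comparison and any planned description by margin; the validity of the main comparison is not in question.

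The power consequence is larger than the imbalance consequence: from 81% to between 52% and 78% one-sided, or from 71% to between 40% and 68% two-sided. These ranges rest on an assumed share of 10–30%, an assumed dCRT survival of 75–85% in that group, 90% in R0 patients and an unchanged 75% after surgery. Stratification would not restore power lost through case mix. If margin-positive patients do as well as R0 patients after dCRT, nothing is lost from this source; the article gives no figure either way.

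**What to change.** 1. In Statistical methods {20a}, stratify the OS and RFS log-rank tests by lateral margin status: negative versus positive or not assessable. State in {16a} whether allocation is already stratified by this factor; if not, stratify the remaining randomisations with a separate envelope set for each margin group. Patients already randomised enter the stratified test using their ESD pathology.
2. Amend {20b} to allow one prespecified, exploratory, descriptive table of OS and RFS by treatment within margin groups, with no claim from an interaction test.
3. In Sample size {14}, say that the 90% comes from an R0/pT1a cohort and is an assumption for the enrolled margin mix, and show power over a range of margin-positive share and survival, as in the table above.

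The Discussion's eligibility rationale needs no change. Cost: a second envelope set, one factor in the tests, one table and a short paragraph; no extra patients or procedures. The downside is that about 3–9 margin-positive deaths (share 10–30%, design survival rates) will give an imprecise estimate, and the table should say so.

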## Trial status

The trial began recruitment in November 2019. The anticipated time of study completion will be December 2027 if necessary. The protocol version 2.0 was discussed on October 25, 2019, by PIs from all participating centers.

## Data Availability

The datasets used or analyzed (or both) during the present study are available from the corresponding author on reasonable request and in ClinicalTrials.gov, NCT04135664.

## Abbreviations

CRC: Clinical research coordinator
CT: Computed tomography
CTV: Clinical target volume
dCRT: Definitive chemoradiotherapy
DMC: Data monitoring committee
EORTC: European Organization for Research and Treatment of Cancer
ER: Endoscopic resection
ESCC: Esophageal squamous cell carcinoma
ESD: Endoscopic submucosal dissection
GTV: Gross tumor volume
JCOG: Japan Clinical Oncology Group
NCCN: National Comprehensive Cancer Network
OS: Overall survival
PI: Principal investigator
PTV: Planning target volume
QLQ-C30: Quality of Life Questionnaire-Core 30
QLQ-OES18: Quality of Life-Esophageal Module 18 Questionnaire
QoL: Quality of life
RCT: Randomized controlled trial
RFS: Relapse-free survival
TSC: Trial steering committee
